### Sample size

The sample size for this study was calculated using the G*Power software (version 3.1.9.7, University of Düsseldorf, Germany). The calculation was based on recent controlled trial studies related to exercise interventions for neck pain [26].Specifically, we employed the F test within the ANOVA framework with an effect size (Cohen’s f) set at 0.4, a significance level (α) of 0.05, and a desired statistical power (1 - β) of 0.8. The calculations determined that a minimum total sample size of 52 individuals was necessary for this study. To accommodate a potential 10% attrition rate, our recruitment target was set at 60 participants, evenly distributed across three groups, with a minimum of 20 participants per group. 

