## Methods

### Study design

This study represents an RCT with three distinct groups: the Daoyin Therapy group (DT intervention), the Meditation + Fitness Exercise group (M + FE intervention), and Control group. The Institutional Review Board approval was obtained from the Shanghai University of Sport (Project Number: 102772023RT016). We originally planned to recruit a total of 60 eligible individuals suffering from CNP who would then be randomly assigned to one of these three study arms, ensuring a balanced distribution among them. Prior to participating in the study, all participantswere required to provide written informed consent. The data collection and analysis for outcomes assessment will be carried out by independent researchers who are blinded to participant allocation. The primary treatment center for this trialis situated at Shanghai University of Sport. A schematic representation of the study design can be found in Fig. 1.

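### The stated ANOVA inputs do not give a minimum of 52 for three arms: they need 64 in total (66 with equal groups), and 52 matches a 1-df test

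*Protocol article*

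**What the plan says.** The Sample size section names the test ("we employed the F test within the ANOVA framework"), an "effect size (Cohen’s f) set at 0.4", "a significance level (α) of 0.05" and "a desired statistical power (1 - β) of 0.8". Its result is: "The calculations determined that a minimum total sample size of 52 individuals was necessary for this study". It then allows for 10% attrition and sets a target of 60, "evenly distributed across three groups, with a minimum of 20 participants per group".

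The Study design section fixes the number of arms ("This study represents an RCT with three distinct groups") and has participants "randomly assigned to one of these three study arms, ensuring a balanced distribution among them".

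The Sample size section does not give the number of groups or numerator degrees of freedom entered in the software. It mentions no repeated measurements and no correlation between them.

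**The concern.** Test, effect size, alpha, power and number of arms are all stated, so the sample size can be checked directly. For three arms the result is too small by 12 (14 with equal groups), which is more than rounding can explain. Because 60 is 52 enlarged for attrition, the recruitment target inherits the error.

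This is the article's only power statement. A reader who accepts 80% power at f = 0.4 will give a non-significant result more weight than the stated calculation supports.

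**Working it through.** **Inputs.** From Sample size: f = 0.4, alpha = 0.05, power = 0.80, attrition 10%, target 60. From Study design: k = 3 arms, balanced.

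**Formula.** For a one-way ANOVA with k groups and total N, the noncentrality is λ = f²N, with df1 = k − 1 and df2 = N − k. Power is the probability that a noncentral F(df1, df2, λ) exceeds the central F critical value at 1 − alpha. Here f² = 0.16.

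**Step 1. What reproduces 52?**

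| Test | N | λ = 0.16N | Power |
|---|---|---|---|
| Two groups, df1 = 1 | 51 | 8.16 | 0.7996 |
| Two groups, df1 = 1 | 52 | 8.32 | 0.807 |
| Three groups, df1 = 1 | 52 | 8.32 | 0.807 |

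With 1 numerator degree of freedom, 52 is the first N to reach 0.80.

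**Step 2. Three groups, df1 = 2.**

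| N | λ = 0.16N | Power |
|---|---|---|
| 52 | 8.32 | 0.707 |
| 54 | 8.64 | 0.726 |
| 60 | 9.60 | 0.776 |
| 63 (21 per arm) | 10.08 | 0.798 |
| 64 | 10.24 | 0.805 |
| 66 (22 per arm) | 10.56 | 0.818 |

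The first N to reach 0.80 is 64. With equal arms it is 66, since 63 just misses. The gaps from 52 are 64 − 52 = 12 and 66 − 52 = 14.

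**Step 3. Attrition.** 52/0.9 = 57.8, so a target of 60 is consistent with its own base, and the error lies in the base. From 66, 66/0.9 = 73.3, so 74, or 75 with equal arms. In the other direction, 60 × 0.9 = 54 completers, 18 per arm.

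**Step 4. Detectable effect.** Solving the three-group power equation for f at power 0.80 gives f = 0.435 at N = 54 and f = 0.411 at N = 60.

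**Step 5. Could a repeated-measures option give 52?** For the between-group factor with m measurements at correlation ρ, λ = f²N·m/(1 + (m − 1)ρ). With m = 3 and ρ = 0.7, the multiplier is 3/(1 + 2 × 0.7) = 1.25. With m = 2 and ρ = 0.6 it is 2/(1 + 0.6) = 1.25. In both cases three-group power is 0.797 at N = 51 and 0.806 at N = 52, so 52 is the first N to reach 0.80. With equal arms the requirement becomes 54 (power 0.823). None of these values of m or ρ is stated in the Sample size section.

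**Step 6. Pairwise contrasts.** In three equal groups, f = 0.4 fixes a range for the largest pairwise difference. If one arm differs from two equal arms, d = 0.4 × 3/√2 = 0.85. If the means are evenly spaced, d = 0.4 × √6 = 0.98. A two-sample t test with 18 per arm and two-sided alpha 0.05 has power of about 0.70 and 0.81 respectively, against 0.726 for the omnibus test. The difference detectable with 80% power is about 0.96 SD, before any multiplicity adjustment.

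**The case against.** The strongest defence is that the section says only that an ANOVA F test was used. It does not say one-way. The planned analyses are longitudinal (repeated-measures ANOVA and GEE over baseline, week 12 and week 16), and a three-group between-factor test can give exactly 52 (Step 5). This stands to the extent that the origin of 52 is unknown. A reader might infer that two groups were entered by mistake. The match with a 1-df test is exact, but the article does not say what was entered, so that remains an inference. The defence does not rescue the paragraph as written: the inputs it lists do not lead to 52 for three arms, and the ones that would are absent.

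A second defence is that the primary analysis is a covariate-adjusted GEE, so the one-way figures are not the trial's real power. That is fair. The article gives no covariate–outcome correlation. Purely as an illustration, one covariate correlated 0.4 with the outcome would bring three-group power at 54 to about 0.80, and 0.5 to about 0.85. The finding therefore concerns the stated calculation, and the power of the planned model is unknown.

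A third objection blocks a stronger reading. A reader might infer that the Daoyin comparisons must have less power than the omnibus test. Step 6 shows that this does not follow: the largest contrast can have power below or above 0.726, depending on the pattern of means. Taking d = 0.8 as the counterpart of f = 0.4 would carry two-group logic into a three-group design.

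That 52 is not divisible by three is only weak support, since it is labelled a minimum total and the target of 60 divides evenly.

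**Conclusion.** The concern holds for the stated derivation. An ANOVA F test with f = 0.4, alpha 0.05 and power 0.80 needs 64 in total for three arms, 66 with equal groups. The stated 52 matches a 1-df test.

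The shortfall at f = 0.4 is moderate. Power is about 7 points below 0.80 at the expected 54 completers (0.726) and 2.4 points below it at 60 with no loss (0.776). No sample size up to the planned 60 reaches 0.80 on this calculation.

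These figures assume a one-way comparison of a single score, equal arms and no covariate adjustment. The documents do not establish that two groups were entered, that the adjusted GEE falls short of 80% power, or that every pairwise Daoyin contrast is weaker than the overall test.

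**What to change.** Correct the Sample size paragraph as follows:

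- Say that, with the stated inputs, the three-group requirement is 66 evaluable participants.
- Say that the planned 60, with about 54 completers, gives about 73% power at f = 0.40, or 80% power at f of about 0.435. Update these figures to the actual enrolment, because the Study design section reports 60 only as the plan.
- If a repeated-measures option produced 52, give the number of measurements and the assumed correlation instead.
- Optionally, add the detectable pairwise difference: about 0.96 SD with 18 per arm, before any multiplicity adjustment.

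The Trial status section places recruitment in March to May 2023, so no extra enrolment is requested. The cost is one reworded paragraph and, unless repeated-measures inputs account for 52, a less favourable power statement. Design, data collection and analysis do not change.

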### Inclusion criteria

The inclusion criteria are: First, potential participants must fall within the age range of 18 to 65 years. They should also have been experiencing neck pain symptoms for a minimum duration of three months. Importantly, candidates should not have a history of prior shoulder or neck surgeries, and they should not present any concurrent shoulder issues. Furthermore, individuals interested in participating should possess a proficient understanding of the Mandarin language, enabling effective communication and the ability to read and write Chinese without any impediments such as dyslexia. In addition, prospective participants should not have been diagnosed with movement disorders and should demonstrate the capability to perform voluntary movements. Lastly, a vital criterion is the expression of a genuine willingness to actively engage and participate in the study, underscoring the importance of their commitment to the research endeavor. 

### Exclusion criteria

The exclusion criteria were individuals with a documented history of whiplash injury, head/neck injuries, or specific disorders affecting the cervical spine, such as disk prolapse, spinal stenosis, postoperative conditions, cervical radiculopathy, or myelopathy. This also extended to individuals with significant spinal deformities, neurological diseases, artificial joints, or metal implants. Additionally, individuals with severe cardiovascular disease or other medical conditions that contraindicated participation in physical activities were ineligible. Those with mental illness or an inability to independently complete the requisite questionnaires due to cognitive limitations were excluded. Participants who had undergone clinical treatment for neck pain in the past three months, were pregnant, had recently given birth, or could not speak or write in Chinese to complete the necessary questionnaires were not considered. Furthermore, individuals who had shown discomfort or aversion towards engaging in regular practice of Baduanjin, Yijinjing, Qigong, or Taichi were excluded. Lastly, individuals demonstrating poor cooperation or a lack of willingness to actively participate in the trial were not eligible for inclusion. 

### Dropout criteria

Participants who do not successfully complete the clinical protocol for specific reasons are classified as dropouts. These reasons include voluntary withdrawal by the participant, typically due to perceived treatment inefficacy or the emergence of adverse reactions. Participants are considered dropouts if they are lost to follow-up, rendering them inaccessible for necessary assessments. In some instances, researchers may opt to remove a participant from the study due to issues related to poor compliance with study protocols or in cases of serious adverse events that mandate discontinuation of their participation.

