### Blinding

Participants were intentionally kept uninformed about the specific type of treatment they would receive throughout the course of the trial. Participants might not have effectively differentiated between DT and the other intervention, making the blinding feasible, except for participants in the control group, as they did not participate in any exercise interventions. A strict blinding protocol was maintained, encompassing outcome assessors, data managers, and the statistician. These key personnel remained unaware of the treatment assignments and did not share any study-related information among themselves. To uphold the blinding process, only the designated coaches possessed knowledge of the treatment allocations. It was imperative that the coaches, who were privy to this information, underwent training to effectively communicate with participants while maintaining the blinding of treatment assignments. This stringent blinding procedure was diligently upheld until the point at which the data were locked, ensuring that the integrity of the trial was preserved and that the results remained unbiased and reliable.

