### Interventions

Participants in the DT and M + FE groups attended their respective training classes three times a week for 12 weeks. Coaches instructed and corrected movements during these sessions, teaching Daoyin, meditation, and fitness exercises. Instructional videos were provided to participants for home practice, and participants could send self-recorded videos to coaches via online communication platforms for feedback. Each DT or M + FE exercise classlasted 40 min continuously, excluding warm-up and relaxation time. Assessments were conducted at baseline, at the conclusion of the 12-week intervention period, and again at the 16-week.

Within each class of the DT group, participants underwent Daoyin exercise tailored for neck pain following a 3-step protocol. This protocol included a 10-min warm-up exercise session involving joint and basic Daoyin exercise to prevent sports injuries. The subsequent 40-min Daoyin exercise session comprised guided single, combination, and full-body movements. Finally, a 10-min relaxation exercise sessionfollowed to soothe and relax the body.

Within each class of the M + FE group, participants received a combination of meditation and fitness exercises designed to address neck pain, following a similar 3-step protocol. The warm-up sessionlasted for 10 min and involved joint exercises and basic limb movements. This was followed by a 40-min session consisting of 20 min of guided meditation activities and 20 min of single, combined, and comprehensive fitness exercises focused on neck pain. Lastly, participants engaged in a 10-min relaxation exercise session.

The control group did not receive any specific intervention but were instructed to continue their daily routines. However, participants in the control group were required to attend health education workshops every 2 weeks as part of their study participation.

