### Statistical analyses

Demographic and baseline information will be compared among the different groups. The Kolmogorov-Smirnov test will be employed to assess the normality of data. For intragroup hypothesis testing, differences across various time points will be evaluated using repeated measures analysis of variance (RM-ANOVA) for normally distributed data, and Friedman’s test will be employed for data not following a normal distribution. In the case of intergroup hypothesis testing, normally distributed data will be analyzed using multivariate analysis of variance (ANOVA), while non-normally distributed data will be analyzed using the Kruskal-Wallis H test. Generalized Estimating Equation (GEE) model will be used to assess how the primary outcome measures, SC-NPAD, change over time across the three intervention groups. Covariates such as demographic factors, and other relevant variables will be included in the model to account for potential confounding effects. The GEE model will also be employed to examine the effects of the intervention on secondary outcome measures, such as SNPA scores for neck and shoulder posture and function, SF-36 scores for quality of life, and levels of neurotransmitters (5-HT, NE/NA, GABA, ACTH, β-EP, and CGRP) obtained from blood tests. Similar to the primary outcome analysis, this analysis will consider the longitudinal nature of the data and adjust for potential confounders. The GEE model will estimate the average change in outcome measures over time within each intervention group and to compare the differences in changes between the intervention groups and the control group. Interaction terms may be included in the model to examine whether the effects of the intervention vary over time or across different groups of participants. Appropriate adjustments for multiple comparisons will be made if necessary. Statistical significance will be taken at 2-sided *P* < 0.05. Statistical analyses will be performed using SAS 9.4 (SAS Institute Inc., Cary, NC).

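### Discretionary removal from the study for poor compliance can end outcome collection unequally between arms and bias the exercise-versus-control comparisons

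*Protocol article*

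**What the plan says.** Four parts of the protocol article bear on this point.

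- **Dropout criteria.** "Participants who do not successfully complete the clinical protocol for specific reasons are classified as dropouts". One listed reason is "voluntary withdrawal by the participant, typically due to perceived treatment inefficacy or the emergence of adverse reactions". Another is a decision by the research team: "researchers may opt to remove a participant from the study due to issues related to poor compliance with study protocols". No level of attendance or adherence is given that would trigger removal.
- **Interventions.** DT and M+FE participants "attended their respective training classes three times a week for 12 weeks". Control participants "were required to attend health education workshops every 2 weeks as part of their study participation".
- **Blinding.** "only the designated coaches possessed knowledge of the treatment allocations". The article does not say who decides on a removal, or whether that person is blinded.
- **Statistical analyses.** "Generalized Estimating Equation (GEE) model will be used to assess how the primary outcome measures, SC-NPAD, change over time across the three intervention groups", with covariates in the model. GEE is also planned for secondary outcomes. RM-ANOVA and Friedman's test are assigned to within-group comparisons over time.

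**The concern.** The rule acts after randomisation, is discretionary, and takes the person out of the study, not only out of the classes. A removed participant would then have no later SC-NPAD score. If those removed differ in outcome from those who stay, and removal is more frequent in one arm, the arms are no longer comparable as randomised.

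The protocol gives grounds to expect both conditions. It says that withdrawal typically follows perceived lack of benefit or adverse reactions, which relates to outcome. Its schedule also gives far more opportunity for poor compliance in the exercise arms than in control. The comparisons at stake are DT versus control and M+FE versus control.

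This is a stated rule, not a detail left to an analysis plan. A plan can define who is analysed, but it cannot supply week-12 and week-16 scores that nobody collected.

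**Working it through.** **The plan's own figure.** Sample size allows 10% attrition on a minimum of 52: 52/0.9 = 57.8, so 58, and the target of 60 covers it (60 x 0.9 = 54). This protects the number analysed. It does nothing about who is lost. The derivation of 52 is a separate matter and is not used here.

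**Compliance burden (Interventions).** Exercise arms: 3 x 12 = 36 classes each. Control: 12/2 = about 6 workshops. The ratio is about 6 to 1. DT and M+FE have the same schedule.

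**Shift from removing the least compliant.** Assume that compliance and outcome are jointly normal with correlation r, that the least compliant fraction q of one exercise arm is removed, and that control loses nobody. The mean outcome of those who remain improves by

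shift = r x phi(c)/(1 - q), in SD units,

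where phi is the standard normal density and c cuts off the tail fraction q.

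| q (of 20) | phi(c)/(1 - q) | r = 0.3 | r = 0.5 |
|---|---|---|---|
| 0.10 (2) | 0.195 | 0.058 | 0.097 |
| 0.15 (3) | 0.274 | 0.082 | 0.137 |

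The values of q and r are assumptions; the protocol gives neither.

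**Scale.** With 20 per arm, the standard error of a difference between two arms is sqrt(2/20) = 0.32 SD. The planned f = 0.4 with three groups means that the squared deviations of the group means sum to 3 x 0.16 = 0.48. The largest pairwise difference d is then sqrt(0.48 x 3/2) = 0.85 SD (two means equal) to sqrt(0.48 x 2) = 0.98 SD (one mean midway). The shift is therefore about 0.2 to 0.4 of a standard error (0.058/0.32 to 0.137/0.32), or 6% to 16% of the planned largest difference (0.058/0.98 to 0.137/0.85).

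**What GEE does with such losses.** A large-sample simulation used 20,000 per arm, no true effect, and correlations of 0.5 between baseline and each later visit and 0.7 between weeks 12 and 16. One arm lost participants after baseline and the other lost none. The table shows the false week-12 effect in the depleted arm in SD units; negative means that it looks better.

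| Loss depends on | Working correlation | 10% lost | 20% lost | 30% lost |
|---|---|---|---|---|
| nothing (MCAR) | either | about 0 | about 0 | about 0 |
| observed baseline (MAR) | independence | -0.08 | -0.13 | -0.18 |
| observed baseline (MAR) | exchangeable | about 0 | about 0 | about 0 |
| unseen week-12 score (MNAR) | independence | -0.13 | -0.26 | -0.37 |
| unseen week-12 score (MNAR) | exchangeable | -0.09 | -0.19 | -0.27 |

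The guarantee for unweighted GEE covers only MCAR, or missingness explained by covariates in the model. In practice a near-correct working correlation removes most of the MAR bias. It does not remove the MNAR bias, and a mixed model would not either. The only full protection is to keep collecting the outcome.

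**The case against.** Several points on the other side are sound.

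- **Data already collected.** A reader might infer that removed participants are excluded altogether and that GEE is run on completers. The article does not say so. GEE can use every available visit, and the full plan may define an as-randomised set. What stands against this is that removal from the study still ends later assessments.
- **Size of the GEE bias.** A reader might take a definite GEE bias as established. Suppose the worst 10-15% at week 12 miss week 16, with correlation 0.6. Independence working correlation gives 0.6 x 0.195 = 0.12 to 0.6 x 0.274 = 0.16 SD, but exchangeable gives about zero. The article names no working correlation, so 0.12-0.16 SD cannot be attributed to the plan.
- **Direction.** A reader might infer that the bias must favour exercise. The control arm receives no specific intervention, so withdrawal for perceived inefficacy could concentrate there and flatter control. Equal outcome-related loss in both arms gives a net bias near zero. The rule also speaks of compliance with study protocols, so the link to class attendance is an inference, and eligibility already screens out people unlikely to cooperate.
- **DT versus M+FE.** The burden is identical, so this argument does not touch that comparison.
- **RM-ANOVA and Friedman.** Their loss of participants with a missed visit concerns within-group tests only, not the comparison between arms.
- **Small-sample standard errors.** An uncorrected sandwich Wald test with 18-20 per arm rejects in about 6-7% of null trials. The article does not specify that test, and an analysis plan could settle it. It is a minor side issue.
- **Timing.** Trial status gives recruitment from March to May 2023, and the abstract says in the past tense that all participants had the week-16 assessment. Collection may be over. The analysis is still described in the future tense, so that part remains open.

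**Conclusion.** The concern holds in a limited form. The protocol permits discretionary removal from the study, without a threshold, for a reason that can arise far more often in the exercise arms, and it expects voluntary withdrawal to be outcome-related. This can bias both exercise-versus-control comparisons. A bias toward exercise is plausible but not shown.

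At 10-15% removal from one exercise arm, none from control, and assumed correlations of 0.3-0.5, the shift is about 0.06-0.14 SD. That is small beside the planned effect, but it is systematic. The simulated MNAR losses give 0.09-0.13 SD at 10% and 0.27-0.37 SD at 30%, a rate well above the attrition that the plan allows for.

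The documents do not support saying that GEE will be biased by a known amount, that collected data will be discarded, or that DT gains over M+FE. The point deserves a change because the rule itself creates the loss and the remedy is cheap.

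**What to change.** **Follow-up**
- Delete poor compliance as a ground for removal from the study.
- Separate stopping the classes from leaving follow-up. This concerns data collection only and leaves the safety provisions for stopping classes as they are.
- Collect SC-NPAD at weeks 12 and 16 from everyone randomised unless consent is withdrawn.
- Where those visits are already past, keep all data obtained and report removals by arm and reason.

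**Analysis**
- Analyse all randomised participants by assigned arm with a likelihood mixed model for repeated measures, unstructured covariance and Kenward-Roger degrees of freedom (PROC MIXED in the SAS release already planned).
- If GEE is kept, combine it with multiple imputation and a small-sample variance correction.
- Add one sensitivity analysis that assumes worse outcomes in those who stopped, because none of these models removes MNAR bias.

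**Cost.** Changes to protocol and analysis wording, questionnaire contact with the few who stop where this is still possible, and a little more analysis work. Estimated effects may look slightly smaller.
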